# TRIAL DESIGN and setting

The EVOCC trial is a two-arm prospective, superiority, multicentre (national), randomised controlled trial (RCT) comparing two modes of treatment which are already routine NHS care, in over30 UK sites (NHS hospitals which already provide care for PAD to patients). Open surgery will be compared to the newer treatment (intervention) using established methodology and pre-specified plans by the CTU team and statisticians. This will address the existing uncertainty whether surgery is superior (clinical and cost-effectiveness) to endovascular treatment. Blinding is impossible in this setting given the completely different nature of the two trial treatments.

Thirty NHS hospital vascular networks which routinely provide care to patients with PAD have confirmed they will take part, across a wide geographical spread (urban and rural); the sites treat a diverse (ethnically and socioeconomically) PAD population, with high prevalence of amputations and diabetes.

The target population is individuals ≥18 years with severe occlusive aorto-iliac disease (TASC II C or D class) presenting with ischaemic lower limb rest pain and/or tissue loss and/or lifestyle limiting claudication to NHS vascular hospital networks. Patients will be screened and recruited across all secondary care settings in those hospitals (clinic, ward, on-call, remote referrals). Randomisation will take place as soon as the patient provides written informed consent. Patients undergoing these treatments in the NHS are usually discussed at multidisciplinary (MDT) team meetings. The patients will be approached for consent once the MDT feel are in equipoise regarding the treatments.

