## Assessment and management of risk

All clinical trials can be considered to involve an element of risk and in accordance to LCTU operating procedures, EVOCC has been assessed for any risks relating uniquely to this trial. Both surgical interventions are routinely used to treat this patient population therefore it has been concluded that the trial carries no higher risk than that of standard medical care.

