# SAFETY REPORTING

## Definitions

| **Term** | **Definition** |
| --- | --- |
| **Adverse Event (AE)** | Any untoward medical occurrence in a patient or clinical investigation participants, which does not necessarily have to have a causal relationship with this treatment.  An AE can therefore be any unfavourable and unintended sign (including an abnormal laboratory finding), symptom or disease temporally associated with the study, whether or not considered related to the study. |
| **Adverse Reaction (AR)** | An untoward and unintended response in a participant to an investigational medicinal product which is related to any dose administered to that participant.  The phrase "response to an investigational medicinal product" means that a causal relationship between a trial medication and an AE is at least a reasonable possibility, i.e. the relationship cannot be ruled out.  All cases judged by either the reporting medically qualified professional or the Sponsor as having a reasonable suspected causal relationship to the trial medication qualify as adverse reactions. It is important to note that this is entirely separate to the known side effects listed in the SmPC. It is specifically a temporal relationship between taking the drug, the half-life, and the time of the event or any valid alternative aetiology that would explain the event. |
| **Serious Adverse Event (SAE)** | A serious adverse event is any untoward medical occurrence that:   - results in death - is life-threatening - requires inpatient hospitalisation or prolongation of existing hospitalisation - results in persistent or significant disability/incapacity - consists of a congenital anomaly or birth defect   Other ‘important medical events’ may also be considered serious if they jeopardise the participant or require an intervention to prevent one of the above consequences.  NOTE: The term "life-threatening" in the definition of "serious" refers to an event in which the participant was at risk of death at the time of the event; it does not refer to an event which hypothetically might have caused death if it were more severe. |

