### Reporting Procedures for Serious Adverse Events

Adverse events which meet the serious criteria (SAEs) and which are deemed related to the trial, except those identified as expected within section 9.1, occurring from point of randomisation and until follow-up completion (minimum of two years after trial treatment), must be reported to the Sponsor and the EVOCC trial management team immediately and within 24 hours of becoming aware of the event. The SAE will be reported using the current standard Sponsor SAE reporting form and according to the Sponsor SOP for reporting serious adverse events. For clarity, those listed in the above table as expected SAEs and SAEs that are deemed as **not** related to the trial do not need to be reported, only those events that fall outside of this list should be reported expediently as described. All exempt SAEs should be recorded in the patient medical notes as such.

**Please note:** **No serious adverse reactions (SARs) are anticipated as a unique consequence of participation in the EVOCC trial.**

The following information will be recorded for all SAEs:

- Description of the event
- Date of onset and end date
- Severity
- Assessment of relatedness to trial
- Action taken.

SAEs will be followed until resolution or the event is considered stable.

It will be left to the investigator’s clinical judgment whether or not an SAE is of sufficient severity to require the participant’s removal from the trial. The participant must undergo an end of trial assessment and be given appropriate care under medical supervision until symptoms cease or the condition becomes stable. The severity of events will be assessed on the following scale: 1 = mild, 2 = moderate, 3 = severe. The relationship of SAEs to the trial will be assessed by a medically qualified investigator.

Additional information will be provided if requested to the Sponsor and main Research Ethics Committee (REC). The Principal Investigator or another delegated physician (as agreed by the Sponsor) is responsible for the review and sign off of the SAE and the assessment of causality.

The Sponsor will perform an initial check of the information and ensure that the SAE line listing is reviewed by the Director of Research & Innovation. All SAE information must be recorded on an SAE form and sent to the Sponsor. Additional information received for a case (follow-up or corrections to the original case) needs to be detailed on a new SAE form and sent to the Sponsor.

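### Section 9 defines causality for a drug and limits SAE reporting to events related to the trial, without saying whether the allocated procedure counts

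*Protocol*

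**What the plan says.** Section 5 describes the trial as "comparing two modes of treatment which are already routine NHS care"; section 7 sets out the two procedures, and neither is a medicinal product.

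Section 9.1 defines an adverse reaction as a response to an "investigational medicinal product which is related to any dose administered to that participant". It explains that this means "a causal relationship between a trial medication and an AE is at least a reasonable possibility", and that the judgement turns on the "temporal relationship between taking the drug, the half-life, and the time of the event". This is the only place where the protocol says what a causal link is.

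Section 9.2.2 sets the reporting rule. An SAE goes to the Sponsor and trial team within 24 hours if it is serious "and which are deemed related to the trial, except those identified as expected within section 9.1". SAEs judged unrelated to the trial are expressly exempt. On who decides, it says: "The relationship of SAEs to the trial will be assessed by a medically qualified investigator". The allocated procedure is not mentioned.

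Two statements colour that rule. Section 8.8 notes that both interventions are routine and that "it has been concluded that the trial carries no higher risk than that of standard medical care". A bold note in section 9.2.2 says that no serious adverse reactions are foreseen as a unique consequence of taking part.

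The end of section 9.2.2 also promises clinical review, within 1 week, of a listing of all SAEs that are life threatening or fatal, and an annual report to the ethics committee listing all SAEs.

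**The concern.** A reporting rule that depends on relatedness needs a definition that investigators can apply. Here the definition supplied does not fit the trial, and the phrase used in the rule is undefined. An investigator facing an unlisted serious complication, such as a late graft infection, has two defensible answers. It was caused by the operation the participant was randomised to, so it is related. Or it is a known hazard of routine surgery that taking part did not add to, so it is not.

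If sites answer differently, the contents of the line listings and the unexpected-SAE table will depend partly on local interpretation. An analysis plan cannot put this right, because it cannot recover reports that sites were told they need not make.

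**Working it through.** No arithmetic applies. The check is to set the sections side by side and see where the two readings lead to different action.

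**1. Does the causality definition fit?** Its elements are an investigational medicinal product, a dose, a trial medication, a product characteristics summary and a half-life. None exists for an aorto-femoral bypass or an iliac stent, so the definition cannot be used for either arm.

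**2. Which way does the rest of the protocol point?**

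| Points to a narrow reading (related means caused by taking part) | Points to a broad reading (related includes the allocated procedure) |
|---|---|
| Section 8.8: no risk beyond standard care | Section 9.1 list: exempts procedural events such as closure-device failure, arterial dissection and puncture-site haematoma, which would need no exemption under the narrow reading |
| Section 9.2.2 bold note: no serious reactions as a unique consequence of participation | Section 11.6.3: unexpected SAEs tabulated by treatment received, in those who underwent trial treatment |
| Section 9.2.2: relatedness judged to the trial, with no mention of the procedure | Section 7 and Table 2: the procedures are called the trial interventions |

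Both columns are in force and no sentence chooses between them.

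**3. Where does the reading change what a site does?** The section 9.1 list holds 44 terms, by count. Sorting serious events by list membership and cause:

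| Serious event | Narrow reading | Broad reading |
|---|---|---|
| On the list | exempt | exempt |
| Off the list, caused by the allocated procedure | exempt | report within 24 hours |
| Off the list, caused by a trial-specific assessment | report | report |
| Off the list, caused by neither | exempt | exempt |

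Only the second row differs. It includes events that the list leaves out by its own qualifiers. Myocardial infarction and heart failure are listed only when non-fatal, and renal replacement only when transient, so their fatal or lasting forms caused by a procedure fall in this row.

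**4. Can the rule feed the promised listings?** Not under either reading. Rows one and four remove listed and unrelated SAEs whatever their outcome. Stroke and bowel ischaemia, for example, are listed with no fatality qualifier. A listing of all fatal or life-threatening SAEs cannot be built from SAE reports that leave these out. The annual report of all SAEs has the same problem.

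**5. What is captured regardless?** Death or major amputation is the primary outcome (section 4.1). Mortality, myocardial infarction, stroke, heart-failure admission, all amputations, re-interventions with their nature and admissions with reasons are secondary outcomes (section 4.2). Section 8.4.2 reviews clinical events at discharge and every later visit. Section 9.1 sends listed SAEs to the routine follow-up CRFs. None of this depends on relatedness. A graft infection that led to re-intervention would be recorded as a re-intervention. Under the narrow reading, what is lost is its expedited report, its causality assessment and its line in the section 11.6.3 table.

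**The case against.** The strongest reply is that the drug wording does no work. The reporting rule in section 9.2.2 never refers to the adverse-reaction definition, the SAE definition needs no causal link, and the adverse-event row already speaks of a relationship with the treatment. That is right: the medicinal-product text is a template remnant. A reader might infer that it screens out every procedural complication, but the documents do not support that.

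A second reply is that the narrow reading sits badly with the protocol as a whole, given the procedural entries in the expected list and the table by treatment received. This also has force, and it suggests that the broad reading was intended. But sites are told in the same section to exempt what is unrelated to the trial, in a protocol that says the trial adds no risk. Intent that must be reconstructed from an exemption list and a table layout is not an instruction.

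Third, the main harms reach the Data Monitoring Committee anyway. Section 10.2 gives it outcome data as well as safety data, and section 11.6.2 has it monitor accruing trial data. This stands and limits the size of the point. The SAE route is not the only safeguard, even without formal stopping rules.

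Finally, selective SAE reporting is a legitimate choice when both treatments are routine care. That is accepted. The difficulty is that the boundary of the selection is not stated.

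**Conclusion.** The point holds as a defect of definition and consistency. The causality wording in section 9.1 cannot be applied to either procedure, the relatedness condition in section 9.2.2 can be applied in two ways, and the listings promised later in section 9.2.2 cannot be met from the SAEs it requires. An amendment is worthwhile because the gap acts at the time of reporting.

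Its reach is narrow: unlisted serious complications of the procedures, and only their expedited reports, line listings and place in the section 11.6.3 table. A reader might infer that hardly any SAE would be reportable, or that some fixed share would be lost. The first requires every site to adopt the narrow reading, against the contrary signals in sections 9.1 and 11.6.3. The second has no basis, since the protocol gives neither a rate of such events nor any indication of how sites will read the rule. Nor does the protocol support a claim that harms vanish from the trial or that the primary comparison is affected.

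The conclusion assumes that sites work from the protocol text; separate SAE form guidance, which is not at hand, could narrow the ambiguity.

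**What to change.** - **Section 9.1:** replace the medicinal-product wording with a definition of a related event: one with at least a reasonable possibility of having been caused by the trial intervention (the allocated open or endovascular procedure) or by a trial-specific assessment, whether or not that procedure or assessment is routine care. Because section 11.6.3 groups by treatment received, state how the definition applies to a participant who undergoes the other procedure.
- **Section 9.2.2:** use the same words in the reporting rule, in the sentence on who assesses relatedness and in the relatedness field of the SAE form. Adjust the bold note so that it cannot be read as limiting the rule.
- **Listings in section 9.2.2:** reconcile the review of all fatal or life-threatening SAEs, and the annual report of all SAEs, with the rule. Either describe them as listings of reportable SAEs or name the other data source that completes them.

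The cost is a wording amendment, one form field, a note to sites and some additional SAE reports. The design, sample size and analysis do not change.

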| **Expected SERIOUS Adverse Events** | The following events are considered as expected SAEs. For the purposes of this trial such events do **NOT** require reporting to the EVOCC central team or Sponsor. These events should continue to be recorded in the medical records according to local practice and on the routine follow-up CRFs.   \| Bowel obstruction \| \| --- \| \| Acute kidney injury \| \| Arterial dissection \| \| Arterial pseudoaneurysm formation \| \| Atrial fibrillation (new) \| \| Bowel ischaemia \| \| Chest infection \| \| Diabetes (new diagnosis) \| \| Diabetic foot ulcer (new) \| \| Diabetic ketoacidosis \| \| Endovascular re-intervention (will have to be reported separately using the relevant form) \| \| Failure of endovascular closure device \| \| Fall \| \| Fasciotomy \| \| Haematoma (at site of surgery or percutaneous puncture) \| \| Heart failure (non-fatal) \| \| Hernia \| \| Hypertension (new diagnosis) \| \| Ileus \| \| Intermittent claudication (new diagnosis) \| \| Laparotomy \| \| Lower limb compartment syndrome \| \| Lower limb oedema \| \| Minor amputation (below the ankle joint) \| \| Myocardial infarction (non-fatal) \| \| Need for open surgical access to an artery during the index endovascular procedure \| \| Peripheral embolisation \| \| Peripheral embolisation, not requiring surgery or re-intervention \| \| Prescription of antibiotics for lower limb tissue loss (ulcer/gangrene) \| \| Re-admission to hospital within 30 days of randomisation \| \| Requirement for catheterisation (urinary catheter) \| \| Stent or graft occlusion \| \| Stent or graft thrombosis \| \| Stoma formation \| \| Stroke \| \| Surgical re-intervention (will have to be reported separately using the relevant form) \| \| Transient ischaemic attack \| \| Transient renal replacement therapy \| \| Urinary retention \| \| Urine infection \| \| Use of additional stent or additional endovascular device \| \| Venous thrombosis (deep and/or superficial) \| \| Viral infection \| \| Wound infection \| |

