### ADVERSE EVENTS REPORTING

Unexpected serious adverse events (SAEs) outside of the list provided in section 9.1, will be reported descriptively in the safety population i.e., participants undergoing trial treatment, presented in groups according to treatment received not as randomised. The number of unexpected serious adverse events and the number of participants experiencing unexpected serious adverse events will be presented categorised by common SAE terms. Unexpected serious adverse events will be presented as line listings and grouped by severity.

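### Section 9.1 exempts any re-admission in the 30 days after randomisation from SAE reporting, so a related event with an unlisted diagnosis can lose prompt reporting because of when the patient came back

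*Protocol*

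**What the plan says.** Section 9.1 defines an SAE by its consequences. One of the qualifying consequences is that the occurrence "requires inpatient hospitalisation or prolongation of existing hospitalisation".

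The same section then gives a table introduced by "The following events are considered as expected SAEs" and says that these events need not be reported to the central team or Sponsor, although they still go in the medical records and on the routine follow-up CRFs. Most entries are diagnoses or complications. One is "Re-admission to hospital within 30 days of randomisation", with no qualifier. Laparotomy also appears without a cause.

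Section 9.2.2 requires a report within 24 hours for SAEs that meet the serious criteria "and which are deemed related to the trial, except those identified as expected within section 9.1". It adds that "only those events that fall outside of this list should be reported expediently as described", and that SAEs judged unrelated to the trial need no report.

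Section 11.6.3 builds the safety tables from the same boundary: "Unexpected serious adverse events (SAEs) outside of the list provided in section 9.1, will be reported descriptively in the safety population".

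**The concern.** An expected-event list is meant to take out known complications so that unexpected ones stand out. That works when each entry names a condition. An entry that names a route of presentation cuts across diagnoses: a graft infection or a gastrointestinal bleed, neither of which is listed, fits the entry as soon as it brings the patient back to hospital inside the window.

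What is at stake is the prompt safety route: the 24-hour report and Sponsor check, the line listings that section 9.2.2 says are reviewed within a week (deaths and life-threatening events) or monthly (others), and the SAE tables. Section 9.2.1 says that AEs are not reported at all, and section 11.6.2 provides no formal interim analysis or stopping rule. Oversight during the trial therefore depends on what reaches the reviewers.

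**Working it through.** No sample-size or power arithmetic applies, and the protocol gives no figure to reproduce. The check is to apply the rules in order to one case and look for text that limits the entry.

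**The case.** A participant has a serious event that the investigator judges related to the trial. Its diagnosis, for example graft infection, is not in the section 9.1 table. It leads to re-admission.

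| Step | Rule | Re-admitted by day 30 | Re-admitted on day 31 or later |
|---|---|---|---|
| 1 | Serious? (9.1) | Yes, hospitalised | Yes, hospitalised |
| 2 | Related? (9.2.2) | Yes, by assumption | Yes, by assumption |
| 3 | Matches a listed entry? (9.1) | Yes, the re-admission entry, read literally | No |
| 4 | 24-hour report? (9.2.2) | No | Yes |
| 5 | In the SAE tables? (11.6.3) | No | Yes |

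The two columns differ only in the date of admission.

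**Text that might limit the entry.** Sections 9.1, 9.2.2 and 11.6.3 do not say that the diagnosis behind a re-admission must itself be judged against the list. Nor is the entry restricted by outcome, although myocardial infarction and heart failure on the same list are exempt only when non-fatal.

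**The clock.** Let *p* be the day of the procedure and *k* the number of days from procedure to re-admission, both counted so that randomisation is day 0. The entry applies when *p* + *k* ≤ 30. Section 5 places randomisation directly after consent, and Table 2 gives no day for the intervention, so *p* is free to vary. Two illustrative values, which are assumptions:

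- *p* = 5, *k* = 20: 5 + 20 = day 25, inside the window, exempt.
- *p* = 40, *k* = 20: 40 + 20 = day 60, outside the window, reportable.

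The interval after the procedure is the same and the classification is opposite. For any participant treated after day 30, the entry can never apply to a post-operative re-admission.

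**Which events are newly exempted.** Unrelated SAEs are exempt anyway under section 9.2.2. Listed diagnoses (wound infection, chest infection, graft thrombosis and so on) are exempt anyway under section 9.1. Off-list events that occur in or prolong the index admission remain reportable, because they are not re-admissions. What remains is the set of events that are related, off-list and the cause of a re-admission inside the window.

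**What is still recorded.** Listed events go on the follow-up CRFs (9.1). Admissions after discharge, with reasons, are secondary outcome 3 (4.2). Admission and death are covered by the clinical event reviews, including the one at day 30 (8.4.2).

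**The case against.** The strongest reply is that an SAE is the untoward occurrence and hospitalisation is only its consequence. On that view the graft infection is the event, it falls outside the list, and it stays reportable whether or not the patient was re-admitted. This reading is open to a site, so it is too strong to say that every unexpected event causing an early re-admission is exempt. But the protocol does not state this reading, and on it the re-admission entry would have little purpose. The rule is at best ambiguous.

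Several larger inferences are tempting and are not supported:

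- **A count of participants.** Assuming that 5% to 20% of the 628 are re-admitted in the window gives 628 × 0.05 = 31 to 628 × 0.20 = 126. The rate is not in the protocol, and the result counts all-cause re-admissions, including unrelated events and listed diagnoses. The relevant number must be smaller and cannot be derived from the document.
- **A biased comparison between arms.** This would need waiting times or lengths of stay to differ by arm, which the protocol does not show. Section 11.6.3 also plans descriptive tables and listings only.
- **That the window covers the period when most events are expected.** Section 11.1 says only that events are more frequent in the first few months after the intervention. It refers to death or amputation, not to SAEs in the 30 days after randomisation.
- **That the re-intervention entries act in the same way.** Both carry a requirement for separate reporting on their own form, so they are not comparable. Laparotomy has no such requirement.
- **That the information is lost.** It is not, as the CRFs, the secondary outcome and the day-30 review show. The DMC also reviews cumulative safety information at least annually.

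**Conclusion.** The point holds in a limited form. One entry on the exempt list is a criterion of seriousness with a time limit, and it has no restriction on cause or outcome. Read literally, it makes reportability of a related, off-list event depend on the date of re-admission. Read generously, it is ambiguous, and more than 30 sites may apply it differently. Its clock runs from randomisation and not from the procedure or discharge, so waiting time enters the classification.

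The size is unknown. The conclusion rests on the wording alone and does not depend on any assumed re-admission rate. What may be lost is the expedited report, the line-listing review and the SAE table entry. This should be corrected at the next amendment, but it does not threaten the primary analysis.

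A separate, smaller inconsistency sits in the same table: myocardial infarction and heart failure are exempt only when non-fatal, while stroke, bowel ischaemia and acute kidney injury carry no such limit, and no reason is given. Deaths are still captured through the primary outcome and secondary outcome 1.

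**What to change.** Either delete the re-admission entry from the section 9.1 list, or state in sections 9.1 and 9.2.2 that a re-admission, and likewise a laparotomy, is exempt only when its underlying diagnosis is itself on the list. Re-admissions would continue to be collected on the CRFs and analysed as a secondary outcome.

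Separately, reconcile the non-fatal qualifiers: explain why they apply to some listed complications and not others, or align those entries for which a fatal outcome is meaningful. A blanket qualifier on every entry would not work, because some, such as a new diagnosis of hypertension or a prescription of antibiotics, cannot sensibly carry one.

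The cost of the main change is a text edit plus some additional SAE forms for related early re-admissions with an unlisted diagnosis. Extending the non-fatal limit to further entries would also bring in forms for related fatal events of those kinds throughout follow-up. Neither change affects treatment, sample size or the primary analysis.
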